## Methods and Materials

### Study Design

The study is a controlled single-center, randomized, parallel group, non-inferiority clinical trial conducted at the Affiliated Hospital of Shandong University of Traditional Chinese Medicine (TCM). An overview of the study visits is shown in **Table 1**, and the study flow chart is highlighted in **Figure 1**.

**Table 1 T1:** Schedule of the study process (SPIRIT Figure).

	Study Period				
	Enrollment	Allocation	Post allocation		
Time point*	1st visit	2nd visit	3rd visit	Pregnancy visit	Follow-up visit
Preconception counselling	**√**	**√**	**√**	**√**	**√**
Eligibility screen	**√**				
Informed consent	**√**				
Questionnaire	**√**	**√**			
Laboratory index measurement (oocyte, zygote, embryo, *etc.*)	**√**				
Serological test for pregnancy		**√**	**√**	**√**	
Allocation (immediate FET or delayed FET)		**√**	**√**		
Menstrual cycle records			**√**		
Transvaginal ultrasound for pregnancy outcomes			**√**	**√**	**√**
Perinatal and neonatal outcomes records				**√**	**√**

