### Statistical Analysis and Sample Size Calculations

#### Estimation of Sample Size

The PASS software version 11.0 (NCSS, LLC. Kaysville, Utah, USA.) will be used to calculate the sample sizes for both groups. Notably, the ongoing pregnancy rate per FET was about 30% based on data from our reproductive center, at the time of the trial design. The calculation revealed that 329 women were to be included in each trial group to provide an 80% power to detect a minimally important absolute difference of 10% points between the immediate and delayed groups for the primary outcome of ongoing pregnancy (40 *vs* 30%) at a two­sided *α* level of 0.05. However, the trial plans to include 732 women, with 366 participants in each arm in order to account for an expected 10% loss to follow-up.

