#### Data Analysis

The intention-to-treat analysis will be used to examine differences in the ongoing pregnancy rate and other secondary outcomes in the two treatment arms during primary analysis. In addition, multiple imputations will be used to process missing values in the data. The demographic characteristics of the two groups will also be compared. Notably, categorical variables will be compared using χ2 analysis while the Student’s t-test will be used to compare quantitative variables. Moreover, multivariable logistic regression will be used to adjust for potentially confounding factors and results, if the randomization fails to achieve two balanced groups. Such factors will include the COH protocol, number of good-quality embryos, female age at oocyte-retrieval day, number of transferred embryos, retrieved oocytes, and quality of the transferred embryos. All statistical analyses will be performed using the SPSS version 26.0 software and a p-value <0.05 will be considered to be statistically significant.

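### The supporting adjusted analysis is a logistic model whose direct result is an odds ratio, while the trial is sized on an absolute 10 points and no conversion is stated

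*Protocol article*

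**What the plan says.** The Study Design section describes a "controlled single-center, randomized, parallel group, non-inferiority clinical trial". Estimation of Sample Size gives the planning rate: "the ongoing pregnancy rate per FET was about 30% based on data from our reproductive center". It expresses the target on one scale only, as "a minimally important absolute difference of 10% points between the immediate and delayed groups", with rates of 40% and 30%, 80% power and a two-sided 5% level. From this come the statements that "329 women were to be included in each trial group" and, after allowing for 10% loss, that "the trial plans to include 732 women, with 366 participants in each arm".

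Data Analysis makes the primary analysis an intention-to-treat comparison of ongoing pregnancy rates, with a chi-square test for categorical variables and multiple imputation for missing values. It adds that "multivariable logistic regression will be used to adjust for potentially confounding factors and results" when randomisation has not produced comparable arms. The listed covariates include age at retrieval, oocyte and embryo counts, and the number and quality of the embryos transferred. No effect measure is named for the adjusted model, and no conversion to percentage points is described. The only decision rule is a p-value below 0.05.

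**The concern.** The target and the adjusted model are both fixed in the article, and they are on different scales. The treatment coefficient of a logistic model is a log odds ratio, conditional on the covariates. Two things separate it from an absolute difference. First, the absolute difference implied by a given odds ratio depends on the control-arm rate. Second, the odds ratio is non-collapsible: when covariates predict the outcome, the conditional odds ratio lies further from 1 than the unadjusted one, even if the arms are perfectly balanced.

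The Discussion section says the trial is meant to reassure clinicians and patients that immediate transfer does no harm compared with delayed transfer. That calls for an interval in percentage points set against a tolerable loss. If the arms look unequal, readers will turn to the adjusted result, and an odds ratio will not tell them directly whether the loss is smaller or larger than 10 points. It could also seem to disagree with the crude result merely because of the scale.

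**Working it through.** **Inputs from the article:** control rate about 30%; difference 10 points; 80% power; two-sided 5% level; 329 per group; 10% loss; 366 per arm.

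**Inputs assumed here, not in the article:** true control rates of 25% and 35%; covariates whose combined effect on the logit scale is normal with SD 0.5 or 1.0.

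**Step 1. Which scale produced the plan's own figure?**
- As worded (40% against 30%, pooled-variance test): n = [1.960·√(2·0.35·0.65) + 0.842·√(0.3·0.7 + 0.4·0.6)]² / 0.10² = 356 per arm, not 329.
- As a non-inferiority size with 30% in both arms, a 10-point margin and one-sided 2.5%: n = (1.960 + 0.842)² · (2·0.3·0.7) / 0.10² = 329.65 per arm, which matches 329 apart from rounding.
- Loss: 329/0.9 = 365.6, so 366 per arm and 732 in total, as stated.

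The arithmetic therefore fits 10 absolute points used as a margin, although the text words it as a difference to detect. On either reading the scale is absolute.

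**Step 2. The 10-point target as an odds ratio at 30%.** OR = [p₁/(1−p₁)] / [p₀/(1−p₀)].
- Loss, 30% to 20%: (0.20/0.80)/(0.30/0.70) = 0.583.
- Gain, 30% to 40%: (0.40/0.60)/(0.30/0.70) = 1.556.

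**Step 3. The same odds ratio at other control rates.** p₁ = OR·o₀/(1 + OR·o₀), with o₀ = p₀/(1−p₀).

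| Control rate | o₀ | 0.583·o₀ | Rate in the other arm | Loss (points) |
|---|---|---|---|---|
| 25% (assumed) | 0.333 | 0.194 | 16.3% | 8.7 |
| 30% (article) | 0.429 | 0.250 | 20.0% | 10.0 |
| 35% (assumed) | 0.538 | 0.314 | 23.9% | 11.1 |

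A confidence limit of 0.583 would thus fall inside 10 points at a 25% control rate and outside it at 35%.

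**Step 4. Effect of prognostic covariates with no imbalance.** For a standard normal x and logit-scale SD s, solve for a so that the mean of 1/(1 + exp(−(a + s·x))) is 0.30. Then solve for b so that the mean of 1/(1 + exp(−(a + b + s·x))) is 0.20. The conditional odds ratio is exp(b).

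| s (assumed) | Conditional OR for a marginal loss of 10 points from 30% |
|---|---|
| 0 | 0.583 |
| 0.5 | 0.569 |
| 1.0 | 0.532 |

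A conditional odds ratio of 0.55 would therefore be a loss of more than 10 points if the covariates had no prognostic value (0.55 is below 0.583), but of less than 10 points at s = 1.0 (0.55 is above 0.532).

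**The case against.** The best case against the point has four parts.

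- Data Analysis names a model and no effect measure. What is reported from a secondary adjusted model is commonly left to the full protocol or the analysis plan, which are not shown. This stands as a reason to keep the point modest. But the article itself fixes both the target and the model, and the model's direct output is off the target's scale, so asking for the two to be aligned is fair.
- The primary comparison is of two unadjusted rates, which give a risk difference directly. This stands in full. A reader might infer that the primary analysis is on the wrong scale, or that the trial's conclusion will rest on an odds ratio. The article supports neither: the logistic model enters only on imbalance, and nowhere is it said to replace the crude result.
- A reader might also infer that the adjusted result can never be set against 10 points. That is too strong. The same logistic model yields an absolute difference once its predictions are averaged, and at exactly 30% with no prognostic covariates the target is simply 0.583 or 1.556.
- With p below 0.05 as the only rule, the null hypothesis of no effect is the same on both scales, so no decision changes. This is true of a test of no difference. It does not help a trial labelled non-inferiority, which needs an interval in percentage points. The absence of a stated margin and interval rule is a separate and larger problem; repairing it on the absolute scale would still leave the adjusted result on another scale.

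The size of the effect also depends on assumptions. Control rates far from 30%, or very strongly prognostic covariates, would make the mismatch look larger, but the article gives no support for them. At an SD of 0.5 the shift is small, from 0.583 to 0.569.

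**Conclusion.** The point holds in a limited form. The target is 10 absolute percentage points, and the only adjusted analysis gives, as its direct output, a conditional odds ratio that cannot be read against 10 points without a conversion the article does not state. Under the assumed control rates of 25% to 35%, the odds ratio that equals a 10-point loss at 30% covers losses from 8.7 to 11.1 points. Under the assumed covariate SD of 0.5 to 1.0, the odds ratio that marks a 10-point loss from 30% is 0.57 to 0.53 instead of 0.583. These shifts matter only for results near the boundary. The crude intention-to-treat comparison, the sample size and the choice of a logistic model are all untouched by this point. It is a worthwhile and inexpensive improvement to the supporting analysis, best made before the data are analysed.

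**What to change.** Keep the logistic model, but state what it reports:

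1. Use only covariates fixed before randomisation. The number and quality of transferred embryos, if they refer to the frozen transfer, are determined after allocation and should be left out.
2. From the fitted model, predict each randomised woman's probability of ongoing pregnancy once under immediate and once under delayed transfer. Average each set over all randomised women, and take the difference in percentage points.
3. Give that standardised risk difference a 95% confidence interval by the delta method or the bootstrap, combined across the multiple imputations.
4. Make it the main result of the adjusted analysis, read on the same absolute scale as the crude risk difference, and show the odds ratio beside it.

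The cost is a sentence or two of analysis wording and a short post-estimation script beyond the default output of the SPSS package named in the article. The design and the sample size do not change.

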## Highlights

The present study is the first randomized controlled trial to attempt to accumulate significant clinical evidence and draw conclusions with regard to the ideal time to conduct FET after a failed fresh embryo transfer cycle.The current protocol includes participants aged 21–44 years, undergoing their first FET after the fixed GnRH antagonist protocol with standard Controlled Ovarian Stimulation (COS) in the IVF/ICSI procedure. The results obtained will therefore be able to reflect the situation in a majority of women in the infertile population.However, it will be impossible to blind the allocation of intervention measures to the participants, physicians, and researchers.The sample size calculation in the current study may also not be able to detect smaller differences in the ongoing pregnancy rates of 10% between the immediate and delayed groups.

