### Randomization

Women undergoing the first FET cycle after a failed-fresh cycle will be randomized into two groups (immediate and delayed) according to a computer-generated randomization list. Randomization will be conducted on the day of the negative blood *β*-hCG test (fourteen days after fresh embryo transfer), for participants with a failed-fresh ET. In addition, randomization will be conducted by the study nurse blinded from the entire recruitment and clinical management of the participants through random number generation and grouping using the SPSS software (Version 26.0, IBM Corp., Armonk). Moreover, the same project nurse will prepare the randomization arm by placing them into opaque envelopes for subsequent use. Finally, participants will be randomized according to the opaque envelopes into one of two groups: 1) The immediate group in which FET will be performed after the first menstrual cycle following the failed-fresh cycle; 2) The delayed group in which FET will be performed after two or more menstrual cycles following the failed-fresh cycle.

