### Interventions

Participants will undergo the IVF/ICSI treatment as clinically indicated. In addition, fixed GnRH antagonist (GnRH-ant) (cetrorelix; Merck Serono, Darmstadt, Germany) protocol will be employed with 150–450 IU/day of recombinant FSH (Puregon, MSD, Courbevoie, France; Gonal-F, Merck-Serono, Lyon, France). Additionally, the doses of gonadotropin will be determined based on the characteristics of individual patients. Thereafter, oocyte retrieval will be conducted under ultrasound transvaginal guidance, 34–36 h after triggering with GnRH-a (Triptoreline, Decapeptyl, Ipsen, France) or recombinant hCG (rhCG, Ovitrelle, Serono, France). Additionally, the BD Falcon IVF medium (Becton, Dickinson and Company, Franklin Lakes, NJ, USA) will be used to collect the oocytes and perform embryo culture at 6% CO_2_, 5% O_2_ and 37.0°C (C200 CO_2_ Incubator, Labotect Labor-Technik-Göttingen GmbH, Göttingen, Germany). After this, oocytes will be fertilized based on the semen quality of individual participants’ partner, using either conventional insemination or ICSI following the standard protocol. Normal fertilization will then be assessed (a second polar body and two pronuclei) after 16–18 h of insemination or ICSI. Notably, an embryo with at least seven blastomeres (grades one and two) on the third day after oocyte retrieval will be defined as good quality. In addition, embryos with fragments <50% will be frozen. According to the standard protocol, all “good” embryos will be vitrified using the cryopreservation method on the third day. Furthermore, patients with more than six good-quality embryos on the third day will be counseled for extended blastocyst and culture transfer.

In addition, a failed-fresh cycle will be defined as a negative *β*-hCG test, fourteen days after fresh embryo transfer. Participants will then be randomized to immediate *versus* delayed groups by specially assigned nurses on the material day. They will also be advised on whether to wait for one or more menstrual cycles after the failed embryo transfer, before the next visit. Moreover, all participants will receive the same treatment before and after the subsequent visit, and there will be no other relevant interventions or concomitant care during the clinical trial. The nurses will inform patients before enrollment that once they are assigned to a group, they will not be able to change unless an unexpected event necessitates the cancellation of embryo transfer.

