Furthermore, the participants’ stress and anxiety levels will be measured using a standard questionnaire before randomization and at the time of commencing FETs. In addition, the Chinese State-Trait Anxiety Inventory will be used to measure the patient’s anxiety levels (26).

On the other hand, Hormone Replacement Treatment (HRT) will be used for endometrial preparation. In addition, treatment with Estradiol valerate will commence on the third day of the menstrual cycle at a dose of 4–6 mg/day for 10–12 days. Moreover, vaginal progesterone (8% Crinone, Merck-Serono, Switzerland) will be administered at a dose of 90 mg per day, after the endometrial layer reaches a thickness of 8 mm as revealed by pelvic ultrasound scanning. FET for day three embryos will also be scheduled on the fourth day after commencing treatment with vaginal progesterone. Furthermore, at least one embryo with the best morphology, will be transferred using a soft embryo-transfer catheter with the guidance of ultrasound. Finally, the serum *β*-hCG levels will be checked fourteen days after FET.

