#### Secondary Outcomes

Positive pregnancy, *i.e.* serum *β*-hCG level ≥10 mIU/ml.Embryo implantation rate: the number of intrauterine gestational sacs observed divided by the number of embryos transferred.Clinical pregnancy, defined as an intrauterine gestational sac with fetal heartbeat detected by transvaginal ultrasonography after 6 weeks of gestation.Ectopic pregnancy, defined as a pregnancy in which implantation takes place outside the uterine cavity.Miscarriage, defined as clinically recognized spontaneous loss of pregnancy before the completion of twenty gestational weeks.Live birth, defined as the birth of at least one child with breath and heartbeat, irrespective of the duration of gestation.Low birth weight, defined as <2,500 g of a newborn’s weight.

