### Data Entry and Quality Control

Embryological laboratory data and treatment-related information including Controlled Ovarian Hyperstimulation (COH) and baseline characteristics will be collected on the day of embryo freezing. On the other hand, data on the FET cycle will be collected on the day of frozen embryo transfer. According to the study protocol, participants’ follow-up data will include that from enrollment and one year onwards. Moreover, patients’ information forms will be retrieved for data entry. Investigators will also be required to ascertain the data accuracy levels (first and second levels), as both levels will include data validation and monitoring, which will be conducted regularly throughout the study by the Data Monitoring Committee (DMC). Data will also be backed up to another computer within the same physical location as the server, on a daily basis.

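### The adjusted model lists the number and quality of transferred embryos as confounders, but on the natural reading both are settled at the frozen transfer, after open allocation

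*Protocol article*

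**What the plan says.** All references are to the protocol article.

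- **Data Analysis.** The intention-to-treat comparison is the primary analysis. Multivariable logistic regression is added to "adjust for potentially confounding factors and results, if the randomization fails to achieve two balanced groups". The covariates are the COH protocol, the number of good-quality embryos, and "female age at oocyte-retrieval day, number of transferred embryos, retrieved oocytes, and quality of the transferred embryos".
- **Randomization.** The time of allocation is fixed: "Randomization will be conducted on the day of the negative blood" β-hCG test, fourteen days after the fresh transfer.
- **Interventions.** For the frozen transfer, "at least one embryo with the best morphology, will be transferred using a soft embryo-transfer catheter". This sets a minimum of one embryo and no maximum. The same section states that "all participants will receive the same treatment before and after the subsequent visit".
- **Data Entry and Quality Control.** Laboratory and baseline data are taken on the day of embryo freezing, whereas "data on the FET cycle will be collected on the day of frozen embryo transfer".
- **Highlights and Blinding.** The article accepts that "it will be impossible to blind the allocation of intervention measures to the participants, physicians, and researchers". Only the embryologist who assesses embryo quality is blinded.

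**The concern.** A covariate that corrects for imperfect randomisation must be fixed before randomisation. Two items on the list appear not to be. How many embryos are transferred, and which ones, is decided at the frozen transfer, at least one menstrual cycle after the envelope is opened. The protocol leaves the number open, and the people who agree on it know the arm.

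This matters in two ways. First, a difference between arms in these variables would be read as failed randomisation, although it may be a consequence of allocation. Second, adjusting for a consequence of allocation changes the question. The adjusted odds ratio no longer estimates the effect of being assigned to immediate or delayed transfer. It could look better or worse for immediate transfer than the randomised comparison does, yet it would be presented as the remedy for imbalance.

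**Working it through.** The plan gives no figure on this point. The check is one of timing, followed by illustrations with assumed effects.

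**1. Timing of each listed covariate**

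| Covariate | When fixed | Before randomisation? |
|---|---|---|
| COH protocol | fresh cycle | yes |
| Female age at retrieval | retrieval day | yes |
| Retrieved oocytes | retrieval day | yes |
| Number of good-quality embryos | assessed on day three | yes |
| Number transferred | day of frozen transfer | no |
| Quality of those transferred | day of frozen transfer | no |

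The frozen embryos available are fixed before randomisation. The selection from them is not. Blinded grading protects the score given to an embryo. It does not make the set transferred a baseline variable.

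**2. What adjustment does**

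Input from the document: ongoing pregnancy 30% (Estimation of Sample Size), used for the delayed arm. Assumptions: 50% of the delayed arm has a multiple transfer, and all log odds ratios below. Let A be the arm (immediate = 1), M multiple transfer and U unmeasured prognosis (0 or 1, half each):

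- logit P(M=1) = dA + g(U − 0.5)
- logit P(pregnancy) = b0 + aA + mM + u(U − 0.5), with b0 set so that the delayed arm has 30%

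| Case | Multiple transfer, delayed → immediate | Risk difference (points) | OR without M | OR with M |
|---|---|---|---|---|
| (i) d=0.8, m=0.5, a=0, no U | 50% → 69% | +2.0 | 1.10 | 1.00 |
| (ii) d=0.8, m=0.7, a=−0.3, no U | 50% → 69% | −3.4 | 0.85 | 0.74 |
| (iii) d=0.8, m=0.5, a=0, u=2, g=−2 | 50% → 65% | +1.5 | 1.07 | 1.14 |
| (iv) d=0, m=0.5, a=0, u=1, g=−1 | 50% → 50% | 0.0 | 1.00 | 1.00 |

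Hand check of (i): b0 ≈ −1.11 gives 24.8% with a single and 35.2% with a multiple transfer. The delayed arm is 0.5 × 24.8 + 0.5 × 35.2 = 30.0%. The immediate arm is 0.31 × 24.8 + 0.69 × 35.2 = 32.0%.

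- In (i), the whole allocation effect acts through embryo number, and adjustment removes it.
- In (ii), adjustment makes immediate transfer look worse than the randomised comparison does.
- In (iii), timing has no direct effect, so 1.00 is the right answer at equal embryo number and 1.07 is the randomised answer. The adjusted 1.14 is neither. Conditioning on M has added bias through U.
- In (iv), allocation does not affect the number, and adjustment does no harm.

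**3. Scale in percentage points**

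Suppose timing has no direct effect, the share with multiple transfer differs by D (immediate minus delayed), and multiple transfer raises the risk by E. The randomised difference is then D × E and the number-adjusted difference is 0, so the adjusted departs from the randomised by −(D × E).

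- D = 0: 0 points
- D = ±10 points, E = 5, 10, 15 points: 0.5, 1.0, 1.5 points, with sign opposite to D
- D = ±30 points (an extreme assumption), same E: 1.5, 3.0, 4.5 points, with sign opposite to D

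For comparison, the 95% half-width with 366 per arm at 30% is 1.96 × √(2 × 0.3 × 0.7 / 366) = 6.6 points.

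No illustration was run for quality. The same reasoning applies to it.

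**The case against.** **The primary analysis is intention-to-treat, and the logistic model is conditional.** This stands. The unadjusted comparison is unaffected, and nothing in Data Analysis lets the adjusted model decide non-inferiority.

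**The arms may not differ in these variables.** The Interventions section commits to equal treatment, describes one endometrial preparation regimen, and has the embryos frozen before randomisation. No mechanism linking timing to embryo number is described. This also stands, and it is why zero distortion is possible. It does not make the variables suitable as confounders, because the number is left open and the choice is unblinded.

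**The trigger may concern baseline imbalance only.** Data Analysis does not say which imbalance starts the model, and the preceding sentences deal with demographic characteristics. On that reading, harm needs two separate events: an imbalance at baseline and an effect of allocation on what is transferred. The listed covariates would still enter the model.

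**Timing at equal embryo number is a sensible clinical question.** It is, as a supportive analysis. Case (iii) shows that the adjusted model need not answer it correctly. The implantation rate, "the number of intrauterine gestational sacs observed divided by the number of embryos transferred", takes account of number, but its denominator is the same post-randomisation variable. It does not repair the adjusted model.

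**The list may mean the fresh transfer.** The text does not say. If so, both variables precede randomisation and the point falls away. The frozen-transfer reading is more natural because the primary outcome follows that transfer.

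**Conclusion.** The point holds in a limited form. On the natural reading, two of the listed covariates are determined after open allocation and cannot show that randomisation failed. If allocation influences them, the adjusted model departs from the randomised comparison in either direction. If it does not, there is no bias. The size cannot be determined from the documents and may be zero. The illustrations rest on assumed effects and only show scale.

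A reader might infer more: that embryo number will differ by arm, or that the adjusted model would produce a false claim of non-inferiority. The documents support neither. The second inference would need an assumed margin, because Estimation of Sample Size presents its 10 points as a difference to detect. It would also need a conversion of the logistic model to a risk difference that is not planned, a large arm difference in embryo number, and a decision taken from the adjusted model instead of the primary one.

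**What to change.** In Data Analysis, restrict the adjusted model to variables fixed before randomisation: female age at retrieval, COH protocol, retrieved oocytes and number of good-quality embryos. All four are already on the list.

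Report the number and quality of transferred embryos by arm as descriptive results. If a model including them is wanted, label it supportive and state that it does not replace the intention-to-treat result. If the fresh transfer is meant, say so.

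No new data are needed, and the change applies equally to women already randomised. The cost is a small loss of precision in the adjusted model, since two covariates that may predict outcome are removed.
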